## Abstract

**Background:**

Total hip arthroplasty (THA) is a very common procedure in orthopedic surgery. In the Netherlands, 25,642 primary THAs were performed in 2013. Postoperative hip dislocation is one of the major complications and has been reported in 0.5 to 10.6 % of patients after primary THA.

Several reports regarding the use of an anterolateral surgical approach have shown that a non-restriction or reduced restriction protocol does not increase the dislocation rate. For the posterolateral surgical approach it has been suggested that patient restrictions might be unnecessary but the amount of available literature is scarce. As such, randomized controlled trials aimed at investigating restrictions following THA using a posterior approach are strongly recommended.

The aim of this prospective randomized controlled trial is to investigate the non-inferiority hypothesis concerning the early dislocation rate after THA in patients with and without the use of a reduced restriction protocol.

**Methods/Design:**

After providing informed consent a group of 456 patients with symptomatic coxarthrosis will be randomized to receive a THA either with care as usual, i.e. receiving postoperative restrictions including the advice to sleep in a supine position for the first 8 weeks postoperatively, or reduced restrictions with no recommendations regarding the position during sleeping. Primary outcome measure will be the percentage of early dislocations within the first 8 weeks after THA. Secondary outcome measures will be patient satisfaction, time to functional recovery, quality of sleep and patient’s self-reported compliance with postoperative instructions.

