**Discussion:**

To our knowledge this will be the first randomized controlled trial that compares a reduced restriction protocol with a restricted protocol following THA using a posterolateral surgical approach. Our hypothesis is that a reduced restriction protocol following THA with use of a posterolateral surgical approach has no influence on the early dislocation rate compared to a restricted protocol. Instead, embracing a reduced restriction protocol might even contribute to a higher quality of sleep, thereby facilitating a faster uptake and return to daily functions in patients after THA.

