## Methods/Design

### Study design

The study design is a single***-***center, parallel-group, stratified, randomized trial with a planned duration of 3 years in which 456 primary THA patients will be allocated to either a care-as-usual group receiving postoperative restrictions including the advice to sleep in a supine position for the first 8 weeks postoperatively or an experimental group, receiving postoperative instructions without restrictions on sleeping position after THA surgery. The experimental group does not use a pillow between the legs in any sleeping position and the care-as-usual group, that is only allowed to sleep in a supine position, is advised to use a pillow between the legs while doing so.

A non-inferiority design was chosen as a standard approach to assess similarity of results of the experimental as opposed to the care-as-usual treatment. In order to avoid an imbalance in treatment assignments and to reduce the opportunity for bias and confounders, a stratified blocked randomization technique will be applied with random sequences of varying block sizes (varying from *n* = 2, *n* = 4 or *n* = 6). Among the stratification factors are operating surgeon and the preferred self-reported sleeping position (supine, prone, on the side, combination/no clear preference) of the patient. Measurements will be taken at baseline (preoperatively), 8 weeks (at regular polyclinic visit) 6, 12 and 24 months after surgery (postoperatively).

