### Secondary study parameters/endpoints

Secondary outcome measures are patient’s compliance with postoperative instructions, the influence of sleeping position restrictions on quality of sleep [18], the influence of sleeping position restrictions on patient satisfaction (anchor questions rating the degree of perceived quality of sleep and burden of the restrictions prescribed, the Client Satisfaction Questionnaire) and the effects of the advice to sleep in a supine position for the first 8 weeks on functional recovery.

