#### The secondary analysis

A repeated measure analysis of (co)variance (ANOVA; group and time) will be applied in order to investigate differences between the groups satisfaction, functional recovery (HOOS) and quality of life (EQ-5D) at 8 weeks, 6 months, 1 and 2 years postoperatively. In addition, correlation coefficients will be calculated between quality of sleep and functional recovery and quality of life. ANCOVA will be conducted dependent upon the analysis of differences in baseline characteristics between groups (e.g. preoperative values, age, radiographic analysis). Subgroup analysis will be directed towards identifying differences in functional recovery between patients with and without compliance and patients who were and were not satisfied.

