Another interestingly aspect of the current study compared to the existing literature is that fact that it incorporates an analysis of the patient self-reported compliance to postoperative restrictions. Our study plans to assess patient compliance to the sleeping position instructions in relation to their preferred sleeping position.

In summary, the aim of this RCT is to show that a reduced restriction protocol following THA with use of a posterolateral surgical approach has no influence on the early dislocation rate. By omitting the postoperative sleeping restriction patients might have a better quality of sleep, higher patient satisfaction and a faster functional recovery. To our knowledge this will be the first RCT that investigates use of a reduced restriction protocol following THA with use of a posterolateral surgical approach.

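### The abstract's time-to-recovery outcome cannot be derived from HOOS scores that start, after surgery, at 8 weeks; the contrast that would show an early benefit is not fixed

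*Protocol article*

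**What the plan says.** All references are to the protocol article.

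- **Abstract, Methods/Design** names a duration, "time to functional recovery", among the secondary outcomes: "Secondary outcome measures will be patient satisfaction, time to functional recovery, quality of sleep".
- **Abstract, Discussion** suggests that the reduced protocol might improve sleep, thereby "facilitating a faster uptake and return to daily functions in patients after THA". The main **Discussion** says that patients might have "higher patient satisfaction and a faster functional recovery".
- **Secondary study parameters/endpoints** has no time element. It lists "the effects of the advice to sleep in a supine position for the first 8 weeks on functional recovery".
- **Study design** gives the schedule: "Measurements will be taken at baseline (preoperatively), 8 weeks (at regular polyclinic visit) 6, 12 and 24 months after surgery".
- **Study procedures** places VAS pain, HOOS and EQ-5D before surgery and again at 8 weeks, with questionnaires at the later times. It also describes a diary of sleeping position, exercise activities and pain, handed in at the 8-week visit.
- **Other study parameters** lists the resumption of activities, with driving as the example.
- **The secondary analysis** equates functional recovery with HOOS: "A repeated measure analysis of (co)variance (ANOVA; group and time) will be applied", covering 8 weeks, 6 months, 1 year and 2 years. Whether ANCOVA is used depends on a comparison of baseline characteristics between the arms.

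**The concern.** One outcome appears in two forms. The abstract promises a duration, while the body and the analysis deal in score levels. The arms differ only in sleeping position, and only for 8 weeks, so any gain in speed should show during that period or at its end. HOOS is not taken between surgery and 8 weeks.

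Recovery is a secondary outcome, but with sleep and satisfaction it is the patient benefit offered as the reason for relaxing the rule. A final report that kept the abstract's wording would have no estimate to put beside it. With the deciding contrast open and baseline adjustment dependent on the data, the same results could also be reported as positive or negative according to which test is read.

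**Working it through.** **Step 1. Can a time to recovery be derived?** It needs a defined event, a date for that event, and observation of the period in which it happens.

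| Need | What the article gives |
|---|---|
| Event | No HOOS threshold or other definition of recovery |
| Date | None assigned to functional recovery |
| Observation before 8 weeks | Diary only (sleeping position, exercise, pain); no function score |
| Method | Repeated-measures AN(C)OVA on scores; no time-to-event method |

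If a threshold were added later, HOOS could place recovery only in one of the intervals 0-8 weeks, 8 weeks-6 months, 6-12 months or 12-24 months. The whole restricted period lies inside the first. The diary and the resumption-of-activities item might hold timing information, but the article ties neither to this outcome nor to an analysis.

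**Step 2. Is there a planned figure to reproduce?** Not for this outcome. The planned 456 patients are sized on dislocation (Sample size calculation: 2.03% against a limit of 6.09%). That gives 190 per arm, 380 in all, and 380 x 1.20 = 456. It does not bear on this point.

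**Step 3. How much does the choice of contrast matter?** The article gives no HOOS effect size or correlation, so these are assumptions: a benefit at 8 weeks only and none later; four postoperative visits with equal variance and a common correlation rho (compound symmetry); two-sided 5%; normal approximation; no baseline adjustment.

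Suppose the 8-week contrast has 80% power. Its noncentrality is 1.96 + 0.84 = 2.80.

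- Group main effect (mean of four visits): the effect is divided by 4, and the standard error is multiplied by sqrt((1 + 3 rho)/4). Noncentrality = 2.80 x 0.25 / sqrt((1 + 3 rho)/4).
- Group-by-time test on 3 df: noncentrality = 2.80^2 x 0.75 / (1 - rho).

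| rho | Main effect: noncentrality | Main effect: power | Group-by-time: noncentrality | Group-by-time: power |
|---|---|---|---|---|
| 0.3 | 0.70/0.689 = 1.02 | 17% | 5.88/0.7 = 8.4 | 68% |
| 0.5 | 0.70/0.791 = 0.89 | 14% | 5.88/0.5 = 11.8 | 83% |
| 0.7 | 0.70/0.880 = 0.80 | 13% | 5.88/0.3 = 19.6 | 97% |

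**Step 4. The same comparison at the trial's size.** Assume 1:1 allocation and a standardised 8-week effect of 0.3, which averages to 0.3/4 = 0.075 over four visits.

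| Per arm | 8-week contrast | Group main effect | Group-by-time |
|---|---|---|---|
| 228 | 89% | 15-21% | 80-99% |
| 182 (20% missing) | 82% | 13-18% | 70-98% |

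The ranges are over rho = 0.3 to 0.7.

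**The case against.** The best defence is that the analysis section does not say what a critic may read into it. It names group and time as factors and lists the separate visits, which fits a group-by-time test or visit-by-visit differences at least as well as an averaged group effect. This stands. A reader might infer that the planned ANOVA dilutes an early benefit over two years. The text does not support that, because nothing makes the group main effect decisive. At correlations of 0.5 and 0.7 the group-by-time test has more power than the 8-week contrast.

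A second defence is that choosing the contrast for a secondary outcome is normally left to an analysis plan, and this is a journal article. Taken alone, that silence would not be a finding. It counts here because the article names an outcome that its analysis cannot deliver, and because it does state a rule for baseline adjustment, a conditional one.

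Third, the expectations of faster recovery are hedged, the stated aim is non-inferiority on early dislocation, and HOOS at 8 weeks followed by later visits can show one arm ahead early and the other catching up. This also stands in part. It would be too strong to say that the trial can learn nothing about faster recovery. What the scores cannot give is a recovery date, or any detail before 8 weeks. The diary and activity items could carry timing, but the article does not assign them to this outcome.

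**Conclusion.** The point holds as a mismatch between outcome, schedule and analysis. The abstract names a time outcome; the body and the analysis define a score outcome, whose first postoperative value coincides with the end of the restriction. As written, no time to recovery can be derived. This conclusion needs no numerical assumption.

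The contrast that tests an early benefit is open, and baseline adjustment is contingent on the data. For a benefit confined to 8 weeks that an 8-week contrast would detect with 80% power, power is about 13-17% if the group main effect is used and about 68-97% with a group-by-time test. The low figures apply only if the main effect were the test and the benefit were gone by 6 months; both are assumptions, as are the correlations and compound symmetry. They show why the contrast should be fixed and are not an estimate of the power of the plan.

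The primary dislocation analysis and the sample size are not affected. The consequence is confined to a secondary outcome, though one that carries part of the patient-benefit argument.

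**What to change.** 1. Drop the time wording from the abstract's outcome list and state the outcome as functional status (HOOS), in line with the endpoints and analysis sections.
2. Prespecify the between-group difference in HOOS at 8 weeks as the key contrast. Estimate it by ANCOVA, or as the 8-week contrast from the repeated-measures model.
3. Always adjust for baseline HOOS and the stratification factors (the article names operating surgeon and preferred sleeping position), whatever the baseline comparison shows.
4. Keep the 6, 12 and 24 month comparisons as planned further contrasts.
5. If a time outcome is wanted, define it as the dated resumption of a named activity. Driving is already the example under Other study parameters. State how the date is recorded and analyse it as time to event.

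Cost: one prespecified contrast and some rewording. Items 1 to 4 need no extra patients or data, but the trial gives up its time-to-recovery wording. Item 5 needs dated records, and the article does not say whether these are collected.

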**Discussion:**

To our knowledge this will be the first randomized controlled trial that compares a reduced restriction protocol with a restricted protocol following THA using a posterolateral surgical approach. Our hypothesis is that a reduced restriction protocol following THA with use of a posterolateral surgical approach has no influence on the early dislocation rate compared to a restricted protocol. Instead, embracing a reduced restriction protocol might even contribute to a higher quality of sleep, thereby facilitating a faster uptake and return to daily functions in patients after THA.

**Trial registration:**

ClinicalTrials.gov NCT02107248, registration date 3 April 2014.

## Background

Total hip arthoplasty (THA) is a very common procedure in orthopedic surgery [1]. In the Netherlands, 25,642 primary THA implants were performed in 2013 [2]. Postoperative hip dislocation is one of the major complications and has been reported in 0.5 to 10.6 % of patient after primary THA [3, 4]. Surgical technique and approach as well as implant selection, implant positioning, patient education and patient-related factors have an impact on the incidence of dislocations [5–7]. Traditionally, patient restrictions following THA are prescribed in order to prevent early dislocation by limiting the flexion of the hip (<90 degrees) as well as adduction and internal rotation [8]. In modern orthopedic surgery, less invasive, tissue-sparing techniques have been introduced and patients are operated upon using shorter acting anesthetics. Nowadays, surgery duration is shorter and patients are being mobilized early after surgery. These factors possibly contribute to less loss of muscle strength after surgery, resulting in a more stable hip joint immediately postoperative. Postoperative joint stability is further enhanced by the use of larger diameter femoral head components. Patients are also better educated and managed with clinical pathways which include detailed protocols, thereby reducing the risk of an early dislocation [6, 9]. However, the aspect of evidence-based application of restrictions after THA has attracted less attention, with long-standing protocols continuing to be routinely used in most hospitals.

Several studies have shown that no or reduced restriction protocols do not result in increased dislocation rates [10–12].

Moreover, Talbot et al. have documented that patients had difficulties sleeping and felt discouraged during the time of restricted postoperative hip precautions [12]. Likewise, faster return to normal activities, higher patient satisfaction and earlier return to work are the benefits that have been shown when using no or reduced restrictions following THA, making it a cost-effective and patient-friendly alternative to the restricted protocol [10, 13]. Nowadays, most of the available knowledge on the effects of reduced postoperative precautions and restrictions after THA has been obtained utilizing an anterior surgical approach [10–12, 14]. This might be explained by the fact that THA utilizing a posterior approach without repair of the posterior capsule and external rotators is associated with an increased risk for dislocation when compared to patients undergoing an anterior or anterolateral approach [15]. However, when conducting a posterior soft tissue repair this “increased” dislocation rate through the posterior approach is reduced [16]. As such, further research on applying a reduced restriction protocol in this group of patients is warranted [17].

To our knowledge this will be the first randomized controlled trial (RCT) that investigates use of a reduced restriction protocol following THA with use of a posterolateral surgical approach. Our hypothesis is that a reduced restriction protocol following THA with use of a posterolateral surgical approach has no influence on the early dislocation rate compared to a restricted protocol.

## Methods/Design

### Study design

The study design is a single***-***center, parallel-group, stratified, randomized trial with a planned duration of 3 years in which 456 primary THA patients will be allocated to either a care-as-usual group receiving postoperative restrictions including the advice to sleep in a supine position for the first 8 weeks postoperatively or an experimental group, receiving postoperative instructions without restrictions on sleeping position after THA surgery. The experimental group does not use a pillow between the legs in any sleeping position and the care-as-usual group, that is only allowed to sleep in a supine position, is advised to use a pillow between the legs while doing so.

A non-inferiority design was chosen as a standard approach to assess similarity of results of the experimental as opposed to the care-as-usual treatment. In order to avoid an imbalance in treatment assignments and to reduce the opportunity for bias and confounders, a stratified blocked randomization technique will be applied with random sequences of varying block sizes (varying from *n* = 2, *n* = 4 or *n* = 6). Among the stratification factors are operating surgeon and the preferred self-reported sleeping position (supine, prone, on the side, combination/no clear preference) of the patient. Measurements will be taken at baseline (preoperatively), 8 weeks (at regular polyclinic visit) 6, 12 and 24 months after surgery (postoperatively).

### Setting

Written informed consent, from patients who meet the inclusion criteria for participation in the trial, having verified that the candidate fully understands what is involved, will be obtained by the research nurse.

Patients will be recruited by the Center for Orthopedic Surgery OCON, Hengelo, The Netherlands. All THAs will be performed by one of OCON’s four orthopedic surgeons specialized in hip surgery and with at least 5 years’ experience in THA. Time, duration and type of anesthesia will be recorded in our patient database. The surgical approach is standard posterolateral with use of a capsular repair. The soft-tissue tension is optimized through neck-length adjustments until an axial force with the leg in extension produces 1 to 2 mm of soft-tissue laxity for male patients and 2 to 3 mm of soft-tissue laxity for female patients.

During trial reduction, stability of the hip is tested in full flexion; 90 degrees of flexion and 45 degrees of internal rotation; full extension; 0 degrees of extension and 45 degrees of external rotation; and with and without knee flexion (up to 90 degrees). Such stability testing is routine in our practice and was not modified for the present study. The implants that will be used are: Exceed ABT Ringloc-XShell, Biomet Orthopedics, E-Poly Hi-Wall Liner Biomet Orthopedics, Modular Taperloc complete femoral stem Biomet Orthopedics, Biolox Delta Modular Ceramic Head 32 mm (Dordrecht, The Netherlands). The postoperative protocol is full weight bearing to tolerance from day 1.

The first radiologic assessment, to control prosthetic positioning occurs on the day of the operation, with an anteroposterior (AP) and lateral view of the hip. The second radiographic assessment is at 8 weeks postoperative with an AP pelvic view and a lateral view of the hip. Implant position including cup inclination angle, acetabular component anteversion, hip offset, and leg length will be measured on the 8 weeks postoperative AP pelvic view. The target zones for anteversion and inclination are defined as 10–30 degrees and 30–50 degrees, respectively.

The local Medical Ethical Committee approves the study design, procedures, protocols and informed consent. The trial is registered at ClinicalTrials.gov NCT02107248.

### Study population

Patients with symptomatic osteoarthritis of the hip who are planned for THA are included if they meet the following criteria: ASA-classification I or II (American Society of Anesthesiologists); written informed consent provided by the patient.

Exclusion criteria are: blindness, scheduled second THA within 6 months, mental incapacity, or inability to fill in the questionnaires in Dutch, infection involvement, wheelchair-dependency, alcohol abuse, and neurological disorders such as Parkinson’s disease, or stroke and hypermobility syndromes such as Ehlers-Danlos syndrome.

### Interventions

After randomization, patients will receive either care-as-usual; postoperative instructions with the advice to sleep in a supine position for the first 8 weeks postoperatively or reduced restrictions; postoperative instructions without any restriction on sleeping position. All patients are instructed by the physiotherapist by oral and written guidelines which include the following:Not to cross the legsNot to squatNot to internally rotate the hip more than 45 degreesNot to flex the hip more than 90 degrees andNot to make a combination of these two movementsWhen sitting not to use a very low chair that makes the hip flex more than 90 degreesWhen sleeping only to sleep in the supine position and to use a pillow between their legs during sleepWhen bending move the operated leg backward so the operated hip will not flex more than 90 degrees

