### Care-as-usual/restricted group

In the restricted group patients have to sleep in a supine position during the first 8 weeks. Hip flexion over 90 degrees and internal or external hip rotation more than 45 is not allowed for the first 8 weeks. Patient will be mobilized by the physiotherapist at the day of the operation or the first postoperative day with full weight bearing to tolerance.

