### Experimental/reduced restricted group

In the reduced restricted group patients are allowed to sleep in any position they find comfortable. Hip flexion over 90 degrees and internal or external hip rotation more than 45 degrees is not allowed for the first 8 weeks. Patient will be mobilized by the physiotherapist on the day of the operation or the first postoperative day. Patient will be mobilized by the physiotherapist at the day of the operation or the first postoperative day with full weight bearing to tolerance.

Patients are instructed by the physiotherapist how to lie in bed and how to prevent more than 90 degrees of hip flexion and 45 degrees of rotation. Next to the general instructions as stated earlier, patients in this experimental group receive additional instructions on how to lie and turn in bed by preventing more than 90 degrees of hip flexion and 45 degrees of rotation.

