### Study procedures

After inclusion and prior to surgery, subject patients will complete the baseline questionnaire at the outpatient clinic during the intake by the nurse practitioner. The physiotherapist will mobilize patients on the day of the operation or the first postoperative day. During this mobilization patients are instructed how turn in bed and how to prevent more than 90 degrees of hip flexion and 45 degrees of rotation. The only difference in instruction between the two study arms is the sleeping position. When discharged to home or nursing home, patients receive a booklet describing the instructions relevant to the study arm they are assigned to. This booklet serves as an enchiridion for partners, physiotherapists, and other persons involved in the care of the patient. In addition, patients are handed a standardized diary booklet in which they are asked to document their sleeping position, exercise activities, experience of pain and any further comments they may want to convey. Patient will visit the outpatient clinic preoperatively and then at 8 postoperative weeks. Routine physical examination will be performed by the orthopedic surgeon. All scores and measurements will be recorded by the nurse practitioner who will also collect the diary booklet from the patients. Preoperative functional assessment will be done by pain severity (Visual Analogue Scale: range 0–10), hip function (Hip Disability and Osteoarthritis Outcome Score) and quality of life (EQ-5D). At 8 weeks follow-up the same functional assessment will be recorded by the nurse practitioner. This visit is combined with the regular postoperative control by the orthopedic surgeon. At 6, 12 and 24 months there will be follow-up questionnaires by Email, paper or telephone depending upon the availability of the patients’ Email addresses. The primary outcome: dislocations within the first 8 weeks, will be recorded in the patient’s file when visiting the emergency department.

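### The protocol contradicts itself on what each arm is told: the instruction list for all patients contains the sleep rule that defines the control arm, and the stated single difference between arms is not the only one described

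*Protocol article*

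**What the plan says.** All references are to the protocol article.

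- **Interventions, opening sentence.** The experimental arm receives "reduced restrictions; postoperative instructions without any restriction on sleeping position".
- **Interventions, list.** "All patients are instructed by the physiotherapist by oral and written guidelines which include the following" introduces a list of movement rules. One item tells patients when sleeping "only to sleep in the supine position and to use a pillow between their legs".
- **Care-as-usual/restricted group.** "In the restricted group patients have to sleep in a supine position during the first 8 weeks".
- **Experimental/reduced restricted group.** Patients may choose any comfortable position. The section refers back to the general instructions as also applying to them, and adds that "patients in this experimental group receive additional instructions on how to lie and turn in bed".
- **Study design.** "The experimental group does not use a pillow between the legs in any sleeping position"; the care-as-usual arm is advised to use one.
- **Study procedures.** "The only difference in instruction between the two study arms is the sleeping position". Just before this, patients are said to be taught turning in bed, with no arm named. At discharge each patient gets a booklet for the assigned arm.

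**The concern.** Two statements about the intervention cannot both be followed. A patient in the experimental arm cannot be told to sleep only supine with a pillow and also be free to choose a position without one. Separately, the claim of a single difference in instruction does not fit the other differences that the article describes.

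This matters more in a non-inferiority trial than in a superiority trial. Anything that makes the two arms alike moves the observed difference toward zero, and here that is the direction of success. The per-protocol population also depends on the answer: it can exclude patients whose position compliance falls below 80 %, and for the experimental arm the text gives two incompatible instructions to comply with. Finally, the Discussion attributes the expected benefit to dropping the sleeping restriction, so the reader needs to know whether anything else was changed with it.

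**Working it through.** **Step 1: set the statements side by side.**

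| Item | Care as usual | Experimental | Where |
|---|---|---|---|
| Position, arm definitions | supine, 8 weeks | free | Study design; Interventions (opening); the two arm sections |
| Position, list for all | supine only | supine only | Interventions (list), applied to the experimental arm by its own section |
| Pillow, arm definitions | advised | none | Study design |
| Pillow, list for all | yes | yes | Interventions (list) |
| Lying and turning in bed | no such item | additional instruction | the two arm sections |
| Turning in bed | taught, arm not named | taught, arm not named | Study procedures |
| Declared differences | sleeping position only | sleeping position only | Study procedures |

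Rows 1 and 2 contradict each other for the experimental arm, and so do rows 3 and 4. The last row conflicts with row 3 and with row 5. Rows 5 and 6 leave open whether in-bed instruction is common, arm-specific, or common with an arm-specific supplement.

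**Step 2: does removing the list item settle it?** Only partly. If the sleep item is a slip, rows 2 and 4 disappear. The arms then still differ in position, pillow and, on the experimental-arm section's wording, in-bed instruction. The single-difference sentence would still be inaccurate.

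**Step 3: direction of the effect if the list were followed literally.** This shows direction only; it is not an estimate.

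The plan's own figure first. Inputs from Sample size calculation: 2.03 % in both arms, limit 6.09 %, one-sided alpha 0.025, power 0.80, 20 % missing data. Margin = 6.09 − 2.03 = 4.06 points.

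n per arm = (1.960 + 0.842)² × 2 × 0.0203 × 0.9797 / 0.0406² ≈ 190. With the allowance for missing data, 190 × 1.20 = 228 per arm, or 456 in total. This matches the plan and does not depend on the present point.

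Now assume, without support in the documents, that the true risk is 6.09 % when free and 2.03 % when held to the supine rule, and that a share c of experimental patients sleep supine because they were wrongly told to. The true difference becomes 4.06 × (1 − c) points. With 190 analysed per arm and an unpooled normal approximation, the chance of declaring non-inferiority is Φ[(4.06 − 4.06(1 − c))/SE − 1.96], with SE in percentage points:

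| c (assumed) | Difference, points | Chance of declaring non-inferiority |
|---|---|---|
| 0 | 4.06 | 2.5 % |
| 0.2 | 3.25 | 6.2 % |
| 0.5 | 2.03 | 21 % |
| 1 | 0 | 80 % |

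The bias runs toward non-inferiority for any c above zero. The documents give no value for c, so the table cannot be read as the size of the problem. At 2.03 %, 190 patients yield about 190 × 0.0203 = 3.9 events, so the approximation is also rough.

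**The case against.** The strongest reply is that the intended comparison is not in doubt. The abstract, Study design, the opening of Interventions, both arm sections, the primary endpoint and the Discussion all describe free versus supine sleep, and the discharge booklets are arm-specific. The likeliest explanation is that the usual-care list was printed without marking its sleep item as belonging to one arm. That stands. A reader might infer from the list that the trial compares something other than what it claims; the documents do not support this.

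The booklet does not remove the conflict by itself. It is handed over at discharge, whereas the list describes the physiotherapist's own oral and written guidelines.

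It can also be said that supine sleep by choice in the experimental arm is part of the policy under test and is not dilution; the trial even stratifies on preferred position, with supine as a category. That is right: only supine sleep caused by a wrong instruction would count. Sleeping position is recorded in the diary, so a collapsed contrast could be noticed.

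On in-bed instruction, both arms carry the same flexion and rotation limits, and Study procedures can be read as teaching turning to everyone. A reader might infer that extra coaching in one arm pulls the result toward non-inferiority. The documents give neither direction nor size for such an effect, and if the instruction belongs to the reduced-restriction policy, its effect is part of the comparison. The pillow difference is openly declared in Study design. What stands is narrower: neither fits the sentence that calls sleeping position the only difference.

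**Conclusion.** The point holds as an internal contradiction in the definition of the intervention. It is a conflict between positive statements, so condensation into an article does not explain it. The list for all patients, carried into the experimental arm by that arm's own section, contains the control arm's sleep and pillow rule. The single-difference sentence disagrees with the pillow difference and with the additional in-bed instruction.

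The consequence is conditional. If the list was followed as written, both arms received the control rule and the comparison is biased toward non-inferiority. The amount cannot be estimated, because it depends on how many experimental patients received and followed that item. If the item is a drafting slip, the contrast is intact and what remains is an inaccurate description of how the arms differ. The text alone does not establish that the wrong contrast was delivered.

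**What to change.** - Reconcile Study design, Interventions, the experimental-arm section and Study procedures, so that one text states which instructions are common to both arms and which belong to one arm. This review takes no view on which instruction is right.
- Check that the physiotherapist's oral and written guidelines and both booklets match the allocation. The article reports recruitment from April 2014, so the check should cover the material already in use and record whether any experimental patients were given the control sleep rule.
- Make the single-difference sentence, and the wording of the trial's conclusion, agree with the differences that remain: sleeping position, pillow and any in-bed instruction.

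The cost is protocol wording and a check of a few documents. Sample size, randomisation and the planned analysis stay as they are.
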